##### Feasibility

Feasibility of the app will be assessed through teacher and parent report using the Feasibility of Intervention Measure [66]. The measure consists of 4 items rated on a 5-point Likert scale ranging from 1 (“Completely disagree”) to 5 (“Completely agree”). The score is calculated by summing all items to yield a total score ranging from 4 to 20, with higher scores indicating greater feasibility of the app. Participants will complete this scale at the end of the trial, 3 months after baseline.

##### Acceptability

Acceptability of the app will be measured through teacher and parent report using the Acceptability of Intervention Measure [66]. The measure consists of 4 items rated on a 5-point Likert scale ranging from 1 (“Completely disagree”) to 5 (“Completely agree”). The score is calculated by summing all items to yield a total score ranging from 4 to 20, with higher scores indicating greater acceptability of the app. Participants will complete this scale at the end of the trial, 3 months after baseline.

##### Appropriateness

Appropriateness of the app will be assessed through teacher and parent report using the Intervention Appropriateness Measure [66]. The measure consists of 4 items rated on a 5-point Likert scale ranging from 1 (“Completely disagree”) to 5 (“Completely agree”). The score is calculated by summing all items to yield a total score ranging from 4 to 20, with higher scores indicating greater feasibility of the app. Participants will complete this scale at the end of the trial, 3 months after baseline.

##### Interview Feedback

Following participation in the study, teachers, aides, and parents will complete a 30-minute interview, where we will gather more context about the usability, feasibility, acceptability, and appropriateness of the KeepCalm app. We will also gather feedback, suggestions, and general impressions about the app. This feedback will also focus on the issue of alarm fatigue, that is, if teachers were overwhelmed, annoyed, or otherwise felt negatively toward the number of notifications received from the app during the day.

#### Secondary Outcome Measures

##### Proximal Preliminary Efficacy Outcomes

*Clinical decision support success*: We will additionally obtain information from teachers to measure the clinical decision support success of the app. This will be calculated from the proportion of alarms and emotion regulation strategy push notifications that result in timely implementation, as measured through in-class observation sessions (if possible, given the COVID-19–related school policies and teacher preferences) and remotely through data entry on the app.

*False positives and false negatives*: False positives and false negatives will be calculated as the proportion of alarms that appear to not be associated with an oncoming challenging behavior (eg, child movement) or challenging behaviors that occurred without an alarm, respectively. This will be measured through in-class observation sessions (if possible, given the COVID-19–related school policies and teacher preferences) and remotely through data entry on the app.

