### Objectives

We present the framework and protocol for a pilot randomized waitlist-controlled field trial that aims to examine the implementation of a digital mental health app, the KeepCalm app (refer to the *Materials* section for details about the app), designed for children on the autism spectrum with challenging behaviors of any IQ or speaking ability. Given that >95% of digital mental health apps have not actually been studied [44,45], an overarching goal of the project is to test the KeepCalm app systematically. We expect the KeepCalm app to score high on usability, acceptability, feasibility, and appropriateness. We also predict satisfactory proximal efficacy (>80% clinical decision support success rates and <20% false positive and negative rates), high technical reliability (the removal of artifacts and offline mode activation success), and the use of the KeepCalm app to result in low severity and frequency of challenging behaviors and emotional dysregulation in children on the autism spectrum after the trial relative to baseline.

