#### HR Stress Zone Tracking

The KeepCalm app pairs with selected commercially available HR trackers (refer to the *HR Trackers* section) that children wear to allow moment-by-moment physiological arousal tracking by educators. After recording a baseline HR for each child, educators are given pop-up notifications to alert them about moderate stress levels, along with individualized top strategies that can be used to reduce their stress. As HR is an index of stress levels [22-24], an increase in HR may index rising stress in children. HR above baseline (ie, HR at rest) is arranged in a stress zone rainbow in the KeepCalm app, with green representing baseline, yellow representing small increase in HR above baseline (+10%), orange representing medium increase in HR above baseline (+20%), and red representing large increase above baseline (+30%). Educators can track the child’s HR, so that they can intervene at moderate stress levels (ie, orange-zone HR) to prevent challenging behaviors associated with high stress levels or HR of approximately 30% above baseline [30] (ie, red-zone HR). In doing so, the educator creates emotion regulation learning opportunities for the child. Increase in HR may occur for other reasons, including increased physical exertion; however, accelerometry data movement thresholds ensure that increases in HR owing to child movement are not reflected in the HR stress zone tracking (refer to the *Offline Mode* section).

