**Proximal preliminary efficacy**																	
	Implementation success	Investigators (classroom observation)									✓						
	False positives and false negatives	Investigators (classroom observation)									✓						

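### The false positive rate is scored on alarms meant to prevent the behavior, so it tends to rise as the strategies work and cannot be read as detector accuracy alone

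*Protocol article*

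**What the plan says.** Under Proximal Preliminary Efficacy Outcomes, the protocol article defines false positives as "the proportion of alarms that appear to not be associated with an oncoming challenging behavior (eg, child movement", and false negatives as "challenging behaviors that occurred without an alarm, respectively". Decision support success is "the proportion of alarms and emotion regulation strategy push notifications that result in timely implementation". These outcomes are to be scored by in-class observation, where school policy and teacher preference allow, and remotely from app entries. Table 1 names only one assessor for them: "Investigators (classroom observation".

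The alarms are not silent. HR Stress Zone Tracking says educators follow the child's heart rate "so that they can intervene at moderate stress levels (ie, orange-zone HR) to prevent challenging behaviors associated with high stress levels". Top Strategy Notifications says the child's top strategies are sent when the orange or red zone is entered.

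Objectives predicts ">80% clinical decision support success rates and <20% false positive and negative rates". Data Analysis, Secondary Outcomes, plans descriptive statistics of these rates and mentions no split by whether a strategy was delivered.

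**The concern.** A false positive rate is normally read as a property of the detector. Here each alarm also triggers an action meant to remove the event against which the alarm is judged. If the alarm was right and the strategy worked, no behavior follows. Unless someone saw that a behavior was building, that record looks the same as a false alarm.

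The article's own premises make this likely to be common. The Introduction says that children on the autism spectrum often do not show emotion in observable ways, and that parents and teachers often report challenging behaviors arising without warning. Observation is conditional. The app entries described under Procedure cover triggers, behaviors, skills and strategies, with no stated entry for an averted episode.

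A low rate could therefore mean accurate alarms or strategies that do little. A high rate could mean poor alarms or strategies that work well. The pilot is meant to inform a fully powered trial, and a misread rate could lead the team to retune an alarm that was working.

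**Working it through.** The article derives no figure for this outcome, so there is nothing to reproduce. The check is algebraic.

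**Inputs**
- s = share of alarms with timely implementation. Set to 0.80, the edge of the prediction in Objectives.
- t = share of alarms that would precede a behavior if nobody acted. Assumed, 0.8 to 1. The Background reports AUC values of 0.71 to 0.82 from previous studies, but an AUC does not give this share.
- e = probability that a delivered strategy averts the behavior. Assumed, 0 to 1.
- q = share of averted episodes counted as false positives. The wording leaves this open, from 0 (all recognized) to 1 (none recognized).
- f0 = share of behaviors missed by the alarm if nothing is prevented. Assumed, 10%.

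Implementation is taken to be equally likely for true and false alarms.

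**False positives**

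Apparent rate = (1 − t) + t·s·e·q.

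With q = 0 this is 1 − t, whatever the strategies do. With q above 0 it rises with both s and e, in proportion to q. At the upper end (q = 1, s = 0.80):

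| t | e = 0 | e = 0.25 | e = 0.50 | e = 0.75 | e = 1 |
|---|---|---|---|---|---|
| 1.0 | 0% | 20% | 40% | 60% | 80% |
| 0.9 | 10% | 28% | 46% | 64% | 82% |
| 0.8 | 20% | 36% | 52% | 68% | 84% |

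For example, t = 0.9 and e = 0.50 give 0.10 + 0.9 × 0.8 × 0.5 = 0.46.

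Under the same scoring, a rate below 20% with s = 0.80 needs e < (1 − 0.8/t)/0.8. That is 0.25 at t = 1 and about 0.14 at t = 0.9. At t = 0.8 or less it cannot be met.

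**False negatives**

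Take all behaviors that occurred as the denominator. Apparent rate = f0 / [f0 + (1 − f0)(1 − s·e)]. With f0 = 0.10 and s = 0.80:
- e = 0.25: 0.10/0.82 = 12%
- e = 0.50: 0.10/0.64 = 16%
- e = 0.75: 0.10/0.46 = 22%
- e = 1: 0.10/0.28 = 36%

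This does not depend on q. Only behaviors that occurred are counted, so prevented ones drop out however the alarm is judged.

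**What a three-class report would show**

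Take 100 alarms with t = 0.9, s = 0.80 and e = 0.50. Of the 90 true alarms, 72 are acted on and 36 of those are averted. Of the 10 false alarms, 8 are acted on.
- Behavior followed: 36 + 18 = 54.
- No behavior, no strategy: 2.
- No behavior, strategy delivered: 36 + 8 = 44.

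The false positive rate then lies between 2% (all 44 counted as true) and (2 + 44)/100 = 46% (all counted as false). The true 10% is inside. Among the 20 alarms not acted on it is 2/20 = 10%, but only because implementation was assumed unrelated to whether the alarm was true.

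**The case against.** The strongest reply is that the definition does not say what the upper-end scoring assumes. It asks whether an alarm *appears* associated with an *oncoming* behavior, and its example, child movement, is a wrong cause of the alarm, not an absent outcome. The same sentence uses *occurred* for false negatives, so the choice of *oncoming* may be deliberate. An observer who saw escalation that a strategy then defused could properly credit the alarm. The app also records triggers, and heart rate before and after a strategy.

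Much of this stands. A reader might infer that every averted episode is scored as a false positive, and the text does not support that. It shows only that q may exceed 0. It does not show that q is 0 either: the judgment needs visible warning signs, which the article says are often absent. A fall in heart rate after a strategy cannot separate an averted behavior from a rise that would have faded anyway.

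A reader might also infer that the plan demands both figures and that an effective app cannot meet both. Objectives predicts them and attaches no go/no-go rule. Even under the harshest scoring, a perfect alarm acted on 80% of the time meets the false positive figure if prevention is below 25%.

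It is also fair that a condensed article may leave coding criteria to a fuller document. Their absence is not the point made here. The article itself states the definition, the reporting and the numeric benchmark. Coding rules could lower q, but they cannot supply warning signs that were not visible, and they leave the false negative effect untouched.

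**Conclusion.** The point holds in a limited form. As described, the false positive rate combines detector accuracy with strategy success, and it tends to rise with effectiveness wherever averted episodes go unrecognized. That pulls against predicting high implementation and a low false positive rate together.

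The direction follows from the definitions once q exceeds 0. The size does not: 20%, 40% and 60% are upper-end values that rest on a perfect alarm, 80% implementation, assumed prevention of 25%, 50% and 75%, and every averted episode counted as false. The false negative rate is inflated whenever strategies prevent alarmed behaviors; an assumed 10% miss share becomes 16% at 50% prevention.

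The outcome is secondary and descriptive in a 20-team pilot, and no primary outcome depends on it. Severity is moderate: the harm is to reading the 20% benchmark and to planning the later trial.

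**What to change.** - Put each alarm in one of three classes: behavior followed; no behavior and no strategy delivered; no behavior and strategy delivered (averted or indeterminate).
- Give the false positive rate as a range, with the third class counted first as all true alarms and then as all false. Read the 20% benchmark against that range.
- Report both rates by whether a strategy was implemented. A missed behavior has no alarm to act on, so for false negatives show how many of the alarmed behaviors in the denominator had a strategy delivered.
- Show figures from observed sessions and from app entries separately, and bring Table 1 into line with the two sources named under Measures.

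The cost is small. Timely implementation is already measured and strategies are already logged, so this is rewording and tabulation, with no change to how alarms are delivered. The rule should be set before scoring starts. The price is a wider and less favorable figure, 2% to 46% in the example above. The rate among alarms not acted on should not be the sole estimate: at the predicted implementation rate fewer than 20% of alarms fall there, and teachers may pass over the ones they believe are false.

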A way to know when a child may be experiencing stress before a challenging behavior, and thus intervene early, is by measuring the physiological state; physiological state is a well-recognized index of stress, which may be captured using many physiological channels, including heart rate (HR) [19-24]. Many theoretical frameworks point to a causal pathway between physiological stress and challenging behavior [8,25-27], and previous studies have shown elevated HR before the onset of a challenging behavior in adults on the autism spectrum [28,29]. In our previous study, we found that there is often a >22% increase in HR in the 58 seconds immediately preceding the challenging behavior and that this increase has moderate utility in predicting challenging behaviors (area under the curve [AUC]=0.72; *P*<.001) [30]. We replicated this finding in 2 samples of children aged 8 to 12 years on the autism spectrum, finding that 33% to 36% increase in HR in the preceding 76 to 80 seconds was associated with challenging behaviors (AUC=0.75-0.82). These results were again replicated in another data set including both children and adolescents on the autism spectrum (AUC=0.71) [31]. These studies suggest that responding to early HR increases may be a more direct approach to identifying the need for emotion regulation strategies, which may support the identification of behavioral triggers.

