Following this training, school personnel participants will begin testing the app within the classroom. They will initially record at least one baseline HR of the child, which will be used to calibrate the app’s stress zone notifications for the child. Baseline HR is recorded over a 5-minute period, during which the child will be engaged in a relaxing activity. We recommend that teachers take 2 to 3 baseline measurements to ensure accuracy. Students will then wear the HR tracker and accelerometer each day during the 3-month testing period. School personnel will be able to track the student’s HR and movement; enter child data about triggers and antecedents, challenging behaviors and skills, and intervention strategies; view the daily report; export the child’s data; and message others on the student’s team. School personnel will receive SMS text message support from the study team during the testing period and will be able to ask questions and troubleshoot any issues that arise during this period. Parents will be able to view the autogenerated daily report for the child, export and build figures of the child’s data, access the intervention strategy resources, and use the app’s messaging features. The research team will remotely monitor each participant’s use of the app during their respective testing period.

Following the app testing period, teachers, aides, and parents will provide feedback about their experience with the app during a brief interview with a member of the research team that will cover various themes including usability, acceptability, feasibility, appropriateness, and any adverse event that may have occurred (the latter will be in addition to the previously mentioned Adverse Events Checklist that will be administered weekly throughout the trial). Measures will be taken at eligibility determination, baseline, throughout the trial, and after the trial as per Table 1. A demographic survey will also be administered at baseline, including a question on the child’s current medications, as some are known to affect HR. If possible, given the COVID-19–related school policies and teacher preferences, the research team will perform in-class observations to obtain a first-hand look at the use of the KeepCalm app in the classroom and to track clinical decision support success and false positives and false negatives (as described in the *Measures* section).

**Table 1 table1:** Timeline for data collection.

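### False alarms are scored by appearance, with no time limit and no chance benchmark, so the rate set against the <20% prediction cannot be interpreted in either direction

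*Protocol article*

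**What the plan says.** Under Proximal Preliminary Efficacy Outcomes, the protocol article defines false positives as "the proportion of alarms that appear to not be associated with an oncoming challenging behavior (eg, child movement" and false negatives as "challenging behaviors that occurred without an alarm, respectively". The word *oncoming* fixes the order of alarm and behavior but not the gap between them. The false negative definition has no look-back period.

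The data come from in-class observation, if school policies and teacher preferences allow it, and "remotely through data entry on the app". Table 1 lists only investigators, by classroom observation, as assessors of this outcome. The Procedure section says the observation sessions serve "to track clinical decision support success and false positives and false negatives", so one session covers both the response to alarms and their correctness. Under HR Stress Zone Tracking, "educators are given pop-up notifications to alert them about moderate stress levels"; the Procedure section has school personnel enter triggers, behaviors and strategies in the app.

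The Objectives predict ">80% clinical decision support success rates and <20% false positive and negative rates". The Secondary Outcomes part of Data Analysis plans descriptive statistics for these rates and mentions no comparison rate.

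**The concern.** Alert accuracy underlies the app's first innovation, and these rates are meant to inform a fully powered trial. A reported figure below 20% would be read as evidence that the alert anticipates behavior, and a figure above 20% as evidence that it does not. Neither reading is safe.

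- **Too lenient.** If a rater may link an alarm to any behavior that follows, some links are coincidence. They are most frequent in children with frequent behaviors and under a broad definition of behavior; the Inclusion Criteria list loud noises and inflexible behavior among the examples.
- **Too strict.** The alert is meant to let staff act before the behavior occurs. If they succeed, there may be no behavior to match, and the alarm may be scored false.

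The text does not say how far each applies. It gives no matching rule, no class for averted episodes and no chance rate.

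**Working it through.** **The plan's own figure.** The <20% prediction comes with no alarm rate, behavior rate or matching window, so it cannot be reproduced. The quantity defined is false alarms divided by all alarms, that is, 1 − positive predictive value, not 1 − specificity.

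**Inputs from the article.** Target: <20%. Lead times in Background: "there is often a >22% increase in HR in the 58 seconds immediately preceding the challenging behavior", and 76 to 80 s for a 33% to 36% rise. Alerts start in the orange zone, at +20%. The top frequency category of the IBR-MOAS runs from about daily to several times a day.

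**Inputs assumed.** Behavior rate L, accepted gap W, and a 6-hour school day. The article gives none of these.

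**Direction 1: chance matches.** Let alarms be unrelated to behaviors, and let behaviors follow a Poisson process at L per hour. An alarm is scored false if no behavior starts within W:

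share scored false = exp(−L·W), below 0.20 when L·W > ln 5 = 1.609.

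| L (assumed) | W = 80 s | 5 min | 15 min | 30 min | 60 min | Gap at which the share is 20% |
|---|---|---|---|---|---|---|
| 0.5/h (3 per day) | 98.9% | 95.9% | 88.2% | 77.9% | 60.7% | 193 min |
| 1/h | 97.8% | 92.0% | 77.9% | 60.7% | 36.8% | 97 min |
| 2/h | 95.7% | 84.6% | 60.7% | 36.8% | 13.5% | 48 min |
| 4/h | 91.5% | 71.7% | 36.8% | 13.5% | 1.8% | 24 min |

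The last column is 60 × 1.609 / L; for 4/h, 60 × 1.609 / 4 = 24.1 min.

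Simulating 10,000 six-hour days, which allows for the end of the day, gives 16.0% false positives and 15.9% false negatives at 4/h each for alarms and behaviors with a 30-min gap. At 1/h each, with any later time that day accepted, it gives 16.6% and 16.8%. At one behavior per day, even if any same-day behavior counts in either order, exp(−1) = 36.8% are scored false and the random alert fails.

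With a fixed window at the article's own lead times, a random alert would need 1.609 × 3600 / 80 = 72 behaviors per hour (80 s) or 1.609 × 3600 / 58 = 100 per hour (58 s) to pass. The accepted gap can therefore decide whether the same random alert passes or fails.

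**Direction 2: prevented behaviors.** Take an alert that is never wrong, so that each alarm precedes a behavior that would otherwise occur. If staff prevent a share q of these and the averted ones are scored false, the measured false positive proportion is q: 10% at q = 0.10, 20% at q = 0.20, 30% at q = 0.30. Preventing 20% or more is enough to miss the target.

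**The case against.** The strongest reply is that a condensed article may leave matching windows, observer forms and masking to a fuller document that is not shown. That would hold if the article were silent. Instead it prints a working rule based on appearance and attaches a numeric prediction to it.

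Other objections stand and limit the point:

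- **Who judges.** Table 1 names investigators as assessors, and nothing says that teachers rule on whether an alarm was false. Staff knowledge of alarms is explicit. Observer knowledge is inferred, because alarm response is tracked in the same sessions and no masking is described.
- **Assumed rates.** At 2 to 4 behaviors per hour, a random alert passes only with gaps of 24 to 48 minutes, which strain the word *oncoming*. At three behaviors per six-hour day the gap is 193 minutes.
- **Stakes.** This is a secondary, descriptive outcome of a pilot, and <20% is a prediction, not a stated go/no-go rule.

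A reader might infer that the rule biases the false positive rate downward, or that an uninformative alert would meet the target. The article supports neither. Prevention pushes the rate the other way, so the net direction is unknown, and passing by chance depends on rates and gaps that the article does not give.

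A reader might also think that counting an alarm as true only if a behavior starts within 80 s would settle the matter. It would score every averted episode as false, and the 80 s figure belongs to a larger heart rate rise than the one that triggers alerts.

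**Conclusion.** The point holds in this form: as written, the false positive and false negative rates depend on rater impression and an unstated gap, have no chance rate beside them, and have no place for alarms that worked. They cannot be read for or against the <20% prediction.

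The size is conditional. A random alert passes only when L·W > 1.61, and it fails at about one behavior per day even under the loosest same-day match. In the other direction, an alert that is never wrong misses the target if it averts 20% or more of behaviors and those alarms are scored false. The chance figures assume independent alarms, Poisson behaviors and assumed rates.

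It should be corrected before data collection, but it does not touch the primary outcomes.

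**What to change.** Replace the appearance-based rule with a timed one:

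1. Where observation takes place, have observers record clock times of behavior onsets and of strategies, without sight of the app or heart rate feed as far as the classroom allows. Take alarm times from the app log.
2. Match by program, with a prespecified primary window informed by the lead times in Background and at least one longer sensitivity window, because alerts start at a smaller rise than the one behind the 80 s figure. Apply a matching look-back window to false negatives.
3. Classify each alarm as followed by a behavior, followed by a strategy and no behavior, or followed by neither. Report the middle class separately, not as false; it may mix averted episodes with unneeded responses.
4. Report false positive and false negative rates with and without the middle class, beside the rate expected by chance from shifting each child's alarm times within the same day.
5. Report app-entry data separately as unmasked. Where observation is not possible, they are the only source.

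The cost is revised wording in Measures, a slightly longer observer form and a short matching program. The article does not say that alarm times are stored or that app entries carry onset times, so both need confirming. The stated rate will probably look less favorable.
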